### Data integrity and management

All collected data are recorded using case report forms which will be processed centrally at the Menzies Institute for Medical Research, University of Tasmania. The hard copies of the case report forms will be stored in a locked area at each study site with secured and restricted access. The electronic data will be stored on password protected servers with restricted access. All data collected will be kept strictly confidential. Daily back ups of all electronic data will occur to minimise any risk of lost data. Data transfer will be encrypted with all data de-identified. Only members of the research team who need to contact study patients, enter data or perform data quality control will have access to patient information.

After study completion, paper copies of data will be archived in secure storage. Identifiers will not be removed, in case follow-up of study patients is necessary; however, electronic data will continue to be kept in a secure electronic database. This will remain password protected and with access given only to the study investigators unless otherwise authorised by the study team.

### Withdrawal

If patients withdraw from the study before 24 months of follow-up, the reason and date will be recorded. Patients who withdraw after a minimum of 9 months will be requested to have a third MRI scan on their study knee.

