**Methods:**

Two hundred sixty-four patients with clinical knee OA, significant knee pain and subchondral BMLs present on MRI will be recruited in Hobart, Melbourne, Sydney and Adelaide. They will be randomly allocated to the two arms of the study, receiving an annual identical intravenous infusion of either 100 mL of fluid containing zoledronic acid (5 mg/100 mL) or placebo (0.9% NaCl 100 mL), at baseline and 1 year later. MRI of the study knee will be performed at screening, month 6 and 24. Knee structure, symptoms and function will be assessed using validated methods. The primary outcome is absolute change in tibiofemoral cartilage volume (mm^3^) over 24 months. Secondary outcomes include improvement in knee pain over 3, 6, 12, 18, and 24 months and reductions in BML size over 6 and 24 months. The primary analyses will be intention-to-treat analyses of primary and secondary outcomes. Per protocol analyses will be performed as the secondary analyses.

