## Background

Osteoarthritis (OA) is a major cause of pain, functional limitations and disability worldwide [1], with hip and knee OA ranked as the 11th highest contributor to global disability and 38th highest in disability-adjusted life years (DALYs) [2]. Current therapies focus on alleviating pain but pain control remains poor in 50% of patients [3]. Furthermore, despite the large disease burden OA has, there are currently no approved disease-modifying OA drugs (DMOADs) that can prevent or stop the joint damage that the disease causes. Therefore, there is a major need to develop new, effective therapies.

The overall lack of treatment efficacy for OA may be partly due to treating everyone as if they have the same pathological process. OA is a complex, heterogeneous disease with multiple phenotypes [4, 5]. Treatment can be optimised by selecting study populations by subgroups with specific features that are likely to respond to particular treatments. One such phenotype is a “bone–specific phenotype” [6].

Subchondral bone marrow lesions (BMLs), visible on magnetic resonance imaging (MRI) have been shown to be an important feature in OA. On MRI they appear as regions of increased signal intensity within the bone marrow, and are a promising target for therapy. In animal models they are the first sign of OA after experimental ligament damage and precede cartilage erosion and degeneration [7]. In humans they are strongly correlated with knee pain [8–10]. Both incident [8] and progressing [10, 11] BMLs are associated with the development of knee pain. Further, a reduction in BML size is associated with pain improvement [11]. Importantly, BMLs are also associated with structural changes. They predict site-specific joint space narrowing (JSN) in those with symptomatic knee OA [12], progression of cartilage defects [13, 14] and cartilage loss on MRI [14–17]. BMLs also predict total knee replacement over periods of up to 4 years [11, 18–22]. In some studies, BMLs predict knee replacements more strongly than other predictors assessed in the same cohort [18, 21].

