### Exclusion criteria

The exclusion criteria were as follows:Prior use of bisphosphonates, except according to the washout schedule:2 years (if use > 48 weeks).1 year (if used > 8 weeks but < 48 weeks).6 months (if used > 2 weeks but < 8 weeks).2 months (if used < 2 weeks).Any intravenous bisphosphonate within the prior 2 years.2)History of non-traumatic iritis or uveitis.3)Abnormal blood tests [serum calcium > 2.75 mmol/L (11.0 mg/dL) or < 2.00 mmol/L (8.0 mg/dL) or creatinine clearance < 35 ml/min].4)Serum 25-hydroxyvitamin D concentrations < 40 nmol/L. Patients with serum 25-hydroxyvitamin D concentrations < 40 nmol/L will have the option to be prescribed vitamin D supplementation and can enter the trial once their serum 25-hydroxyvitamin D concentration level is ≥40 nmol/L.5)Use of any investigational drug(s) and/or devices within 30 days or 5 half-lives (whichever is longer) of the drug prior to randomisation.6)Prior diagnosis of cancer (metastatic cancer or cancer diagnosed < 2 years ago where treatment is still ongoing).7)Poor dental fitness: A dental exam with appropriate preventative dentistry will be considered prior to treatment with bisphosphonates in patients with concomitant risk factors (e.g. cancer, chemotherapy, corticosteroids, poor hygiene).8)Severe knee OA (JSN on X-ray of Grade 3 using the Osteoarthritis Research Society International (OARSI) atlas [43]).9)Other forms of arthritis in which disease is active and concomitant medication is used (e.g. rheumatoid arthritis or other inflammatory arthritis).10)Patients who have undergone arthroscopy or open surgery in the index knee in the last 12 months.11)Women who are pregnant or breast feeding.12)Patients who have had a corticosteroid injection in the last 3 months or a hyaluronic acid injection in the last 6 months in the index knee.13)Planned joint replacement surgery.14)Contraindication to MRI scanning (for example, implanted pacemaker, metal sutures, presence of shrapnel or iron filings in the eye, claustrophobia, knee too large for coil).15)Inability to give informed consent.

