### Study procedure and time points

Research nurses will first conduct screening over the telephone. If early checks of study eligibility are favourable, study patients will be booked in for a face-to-face screening visit to further determine eligibility and explain what is involved in the study. At the face-to-face visit, patients will complete questionnaires, have a knee x-ray and MRI, a blood test, and a clinical assessment by a study doctor to ensure inclusion criteria are met. The study knee will be defined as the one with symptomatic OA meeting all inclusion criteria.

Table 1 outlines the schedule of assessments. After screening, there will be 4 study visits (month 0, 6, 12 and 24). The same researcher nurses, who are blinded to treatment allocation, will measure all clinical variables, administer questionnaires, monitor compliance, and record adverse events at these visits. Additional questionnaire mail outs will occur at months 3 and 18. Infusions will occur at months 0 and 12; MRI scans will occur at screening, month 6 and 24; knee x-ray will be performed at screening; blood samples are taken at screening and 6 months, and urine samples are taken at baseline and 6 months. Three days following the infusion, patients are contacted by phone interview to assess side effects of acute phase reactions.

**Table 1 Tab1:** Schedule of assessments

	Screening	Baseline (Month 0)	Day 3 Post-Infusion	Month 3	Month 6	Month 12	Day 3 Post-Infusion	Month 18	Month 24
Informed consent	x								
Clinical examination	x								
Knee x-ray	x								
Bloods	x				x*				
Knee MRI	x				x				x
Randomisation		x							
Clinic measures									
Leg strength		x			x	x			x
Height and weight		x			x				x
First void fasting urine		x*			x*				
Infusion		x				x			
Questionnaire measures									
Demographics (sex, date of birth)	x								
Knee VAS	x	x		x	x	x		x	x
Knee WOMAC		x		x	x	x		x	x
Medication use	x			x	x	x		x	x
Knee surgery	x			x	x	x		x	x
Knee joint injection					x	x		x	x
Safety (adverse events)		x	x	x	x	x	x	x	x
Acute phase reactions			x				x		
Hand VAS		x		x	x	x		x	x
Back VAS		x		x	x	x		x	x
AQoL-4D		x			x				x
Overall change in pain and function									x
Treatment guessing									x

*Only being performed at the Hobart, Melbourne and Sydney study sites

*MRI* magnetic resonance imaging, *VAS* visual analogue scale, *WOMAC* Western Ontario and McMasters Universities Osteoarthritis Index, *AQoL-4D* The Assessment of Quality of Life

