Melbourne	3.0 T whole-body MR unit (Philips, Achieva, Medical Systems), using a commercial 16-channel transmit receive knee coil	T1-weighted fat-saturated 3D gradient-recalled acquisition; flip angle 15 degrees; repetition time 25.9 msec; echo time 9.2 msec; field of view 16 cm; 320 × 320 matrix; slice thickness 0.5 mm	Proton density fat-saturated 2D fast spin echo sequence; flip angle 90 degrees; repetition time 3814 msec; echo time 25 msec; field of view 16 cm; 720 × 720 matrix; slice thickness 2.5 mm
Sydney	1.5 T whole-body MR unit (Siemens, Aera) using a dedicated 15-channel transmit-receive knee coil	T1-weighted fat-saturated 3D gradient-recalled acquisition; flip angle 30 degrees, repetition time 31 msec; echo time 6.8 msec; field of view 16 cm; 512 × 512 matrix; slice thickness 1.5 mm	Proton density fat-saturated 2D fast spin echo sequence; flip angle 150 degrees; repetition time 3830 msec; echo time 39 msec; field of view 16 cm; 512 × 512 matrix; slice thickness 3 mm
Adelaide	1.5 T whole-body MR unit (Siemens, Aera) using a dedicated 15-channel transmit-receive knee coil	T1-weighted fat-saturated 3D gradient-recalled acquisition; flip angle 30 degrees, repetition time 14.7 msec; echo time 6.74 msec; field of view 16 cm; 448 × 448 matrix; 1 excitation; slice thickness 1.5 mm	Proton density fat-saturated 2D fast spin echo sequence; flip angle 180 degrees; repetition time 3200 msec; echo time 39 msec; field of view 16 cm; 320 × 320 matrix; 1 excitation; slice thickness 3 mm

Knee femoral cartilage volume will be determined on the sagittal T1-weighted sequences by means of image processing on an independent workstation using Cartiscope™ (ArthroLab Inc., Montreal, Quebec, Canada), as previously described [46–48]. The segmentation of the cartilage-synovial interfaces will be carried out with the semi-automatic method under reader supervision and with corrections when needed. Cartilage volume will be evaluated directly from a standardised view of 3D cartilage geometry as the sum of elementary volumes. In our previous study, we demonstrated a CV of approximately 2% [46]. The cartilage volume assessment will be done for the medial and lateral condyles delineated by the Blumensaat’s line [48].

Tibiofemoral cartilage volume will be calculated as the sum of both the tibial and femoral compartments at screening and 24 months.

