##### Knee surgery and joint injections

Whether the patient underwent any knee surgery (including arthroscopies or joint replacement surgery) during the trial, will be assessed by questionnaire at screening, month 3, 6, 12, 18 and 24 months. Study patients will also give their consent to have their data linked to the Australian Orthopaedic Association National Joint Replacement Registry (AOANJRR). Whether the patient had a joint injection during the trial will be assessed at month 6, 12, 18 and 24 months.

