### Statistical analysis

The primary analyses will be intention-to-treat analyses of primary and secondary outcomes. Per protocol analyses will be performed as the secondary analyses.

Changes in absolute tibiofemoral cartilage volume, knee pain and BML size will be analysed using a linear mixed model with treatment, month and their interaction (treatment × month) as covariates. The correlation within trial centres and the repeated measures will be addressed using trial centre and patient identification as random intercepts. Month will be treated as random effect to allow different treatment effects among patients over time. Change in outcome measures within each group and difference of the changes between groups from baseline to follow-up will be calculated using linear combinations of the estimated coefficients. If there are baseline imbalances between treatment groups, we will consider adjusting for them based on whether we regard the imbalance as clinically significant. Missing data caused by loss to follow-up and nonresponses will be addressed by adding baseline complete variables that can explain the missingness to the regression models.

Secondary analysis for missing data will be performed using multiple imputation by chained equations. Baseline variables with complete data will be used for data imputation assuming missing at random.

Pre-specified stratified analyses will be performed to examine which subgroups may respond better to treatment. Potential stratification variables include radiographic knee OA and co-pathology present on MRI. Statistical significance will be set as a two-sided *P* value < 0.05.

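### The only unscheduled MRI is tied to withdrawal from the study, so a patient whose study knee is replaced during follow-up loses the primary outcome, probably in an informative way

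*Protocol article*

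**What the plan says.** All references are to the protocol article.

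- **Outcome** (Abstract, Methods): "The primary outcome is absolute change in tibiofemoral cartilage volume (mm^3^) over 24 months".
- **When it is measured** (Primary outcome measure): "Tibiofemoral cartilage volume will be calculated as the sum of both the tibial and femoral compartments at screening and 24 months". Under Study procedure and time points, "MRI scans will occur at screening, month 6 and 24", but the month-6 scan is not named for cartilage volume.
- **Off-schedule scans** (Withdrawal): "Patients who withdraw after a minimum of 9 months will be requested to have a third MRI scan on their study knee". No other trigger is given.
- **Surgery** (Other measurements, in the part on operations and injections): "Whether the patient underwent any knee surgery (including arthroscopies or joint replacement surgery) during the trial, will be assessed by questionnaire". The question is put at screening and at months 3, 6, 12, 18 and 24, with consent to linkage to the national joint replacement registry. No scan is attached to a report of surgery.
- **Missing data** (Statistical analysis): "Missing data caused by loss to follow-up and nonresponses will be addressed by adding baseline complete variables that can explain the missingness". The secondary approach is multiple imputation from complete baseline variables under missing at random.
- **Link to progression**: the Background says "BMLs also predict total knee replacement over periods of up to 4 years", and a BML is an entry requirement. The Discussion adds that MRI-measured cartilage loss itself predicts knee replacement.
- **Entry limits** (Exclusion criteria): "Planned joint replacement surgery" and OARSI grade 3 joint space narrowing are both excluded.

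**The concern.** Take a patient whose study knee is replaced at month 15 and who keeps attending. The patient has not withdrawn, so the Withdrawal rule asks for no scan. The surgery question concerns operations already done. At month 24 the native cartilage is gone, and the primary outcome cannot be measured then or later. A replacement before month 9 is not covered even if the patient does withdraw.

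Most missing-data questions can be left to an analysis plan. This one cannot be fully settled there, because the measurement must be taken before the operation or it does not exist.

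The loss is unlikely to be random. On the article's own account, knees that lose cartilage faster are more likely to be replaced, and that loss occurs after baseline. Adjusting for or imputing from baseline variables does not use it. The article also hopes that an effective drug would delay or reduce replacement. If so, more fast-losing knees disappear from the placebo arm than from the active arm, and the observed structural benefit shrinks. If replacement differs between arms by chance, the bias follows that imbalance.

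**Working it through.** **1. The plan's own figure.** From Sample size calculations: expected change −824.0 mm³ (SD 273.0) on active and −928.3 mm³ (SD 272.3) on placebo, 132 per arm, 20% dropout, 80% power, two-sided 5%.

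- Difference = 928.3 − 824.0 = 104.3 mm³. Pooled SD = √[(273.0² + 272.3²)/2] = 272.65.
- n per arm = 2 × (1.960 + 0.842)² × 272.65² / 104.3² ≈ 107.3, so 108.
- With dropout: 108/0.8 = 135, or 108 × 1.2 ≈ 130. The stated 132 lies between them.
- Power at 132 × 0.8 = 105.6 completers per arm = 79.4%.

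The sample size reproduces and is not disputed. It leaves no spare power.

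**2. Assumptions for the bias.** The article gives no replacement rate. Assumed proportions replaced (placebo v active): 3% v 1% and 5% v 2%, which is about 4 v 1 and 7 v 3 knees of 132. Outcomes are taken as normal with the article's SDs. Let ρ be the correlation between a knee's tendency to be replaced and its true cartilage loss: ρ = 1 means only the fastest losers are replaced, ρ = 0.5 is moderate selection, and ρ = 0 is none.

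**3. Formula.** If a proportion p is removed from an arm, with z the upper-p normal quantile and φ the normal density:

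- mean excess loss of the removed knees = ρ × SD × φ(z)/p
- reduction in the mean loss of the remaining knees = ρ × SD × φ(z)/(1 − p)
- hidden difference = placebo reduction − active reduction

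**4. Results.**

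| Rates | ρ | Placebo reduction (mm³) | Active reduction (mm³) | Hidden (mm³) | Share of 104.3 |
|---|---|---|---|---|---|
| 3% v 1% | 1 | 272.3 × 0.0680/0.97 = 19.1 | 273.0 × 0.0267/0.99 = 7.3 | 11.8 | 11% |
| 5% v 2% | 1 | 272.3 × 0.1031/0.95 = 29.6 | 273.0 × 0.0484/0.98 = 13.5 | 16.1 | 15% |
| 3% v 1% | 0.5 | 9.6 | 3.7 | 5.9 | 6% |
| 5% v 2% | 0.5 | 14.8 | 6.7 | 8.0 | 8% |

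With equal rates (3% v 3% or 5% v 5%) the hidden difference is below 0.1 mm³ in absolute size. With ρ = 0 it is zero and only patients are lost.

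**5. Cross-check by simulation.** Here the same surgery threshold applies in both arms, so the active-arm rate follows from the planned effect. Replaced knees are lost on top of the 20% dropout.

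| Assumed placebo rate | ρ = 0.5: difference, power | ρ = 1: difference, power |
|---|---|---|
| 2% | 102.3 mm³ (−2%), 78% | 97.0 mm³ (−7%), 76% |
| 5% | 99.9 mm³ (−4%), 76% | 89.2 mm³ (−14%), 72% |
| 10% | 97.6 mm³ (−6%), 73% | 80.4 mm³ (−23%), 65% |

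The 5% row agrees in scale with step 4. The 10% row shows what a rate above the main assumption would do.

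**The case against.** **Few knees may be affected.** Excluding planned replacement and grade 3 narrowing removes the knees nearest to surgery, the rates above are assumptions, and placebo is always set above active. This stands. It is why the effect is called modest, but it does not prevent surgery that arises over 24 months.

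**An article condenses.** Withdrawal is two sentences long, and Quality assurance refers to a protocol book with visit and measurement detail, which may contain a scan rule for surgery. That is possible. But the article does state a rule with a specific trigger, and as stated the trigger is too narrow.

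**Sites may hear of surgery in advance.** Safety assessment describes regular visits, calls between visits and spontaneous reporting. A reader might infer that sites always learn too late, and the article does not show that. What stands is that no scan is tied to such notice. A patient who withdraws after month 9 because surgery is planned could be scanned in time, but the text does not set that timing.

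**Replacement is not purely progression.** Symptoms and patient choice also matter, so faster loss in replaced knees is a tendency supported by the Discussion, not a certainty. This is why moderate selection is shown beside the extreme case.

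**A larger bias might be inferred.** Suppose replaced knees lose an extra amount equal to the whole planned placebo mean, about 928 mm³. At 5% v 2% that hides 0.03 × 928 ≈ 28 mm³, or 27% of 104.3. The article's own SD does not support this: 928/272.3 = 3.4 SD, while the fastest-losing 5% of placebo knees average only 272.3 × 0.1031/0.05 ≈ 562 mm³ above the mean.

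**Pain might be drawn in.** A reader might infer that low pain scores from a replaced knee will be counted as drug benefit. The article does not say so. It specifies intention-to-treat analysis and is silent on scores after surgery, which an analysis plan not shown may settle. The issue does not follow from the scan rule, and no claim about pain is made here.

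**Conclusion.** The point holds in a narrow form. The Withdrawal trigger misses an event that permanently destroys the primary measurement, and on the article's own account that event is related to the outcome. Baseline-only methods under missing at random cannot be expected to correct it.

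The size is probably modest and rests on assumed rates. At 3% v 1% to 5% v 2% replaced, about 6% to 8% of the planned difference is hidden under moderate selection, with a ceiling of about 11% to 15% under perfect selection. The bias is near zero if rates and excess loss are equal across arms. If the drug works as hypothesised, it runs toward no benefit. This does not invalidate the trial or its sample size. It is worth correcting because power is already just under 80% and the repair is cheap.

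**What to change.** 1. **Withdrawal**: request that the 24-month MRI be brought forward to before the operation for any patient listed for replacement of the study knee, whether or not the patient withdraws and without the 9-month minimum.
2. **Knee surgery and joint injections, and Table 1**: ask at each contact about planned as well as completed study-knee surgery, so that sites have notice.
3. **Statistical analysis**: enter these scans at their actual date instead of as month 24. The existing withdrawal scans need the same treatment.

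**Cost**: one extra questionnaire item and an already planned scan moved earlier for a few patients. The downside is a shorter measurement interval for those patients, so their change has to be interpreted through the model's time trend. Some operations will still occur without notice, and those knees will remain missing.

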### Roles and responsibilities and monitoring

The University of Tasmania (as the trial sponsor) and the principal investigators are responsible for all aspects of the trial, including design, conduct and oversight. The principal investigators will monitor the conduct and progress of the project at each site. The trial coordinator will visit each study site to make sure that all trial procedures are compliant with the trial protocol. The principal investigators and the research team will have regular teleconferences to ensure efficient study execution and ongoing monitoring of the study progress, with summary documents circulated after each meeting. A Data and Safety Monitoring Board was not convened for this trial as zoledronic acid is approved in Australia by the Therapeutic Goods Administration (TGA) and has a well-known safety profile. The trial is also being monitored at each site by a practicing rheumatologist with experience prescribing zoledronic acid.

